## Analysis

**Primary outcome:** The primary outcome is treatment failure (as defined above) at 15 months. Those assessed as “Definite success” and “Probable Success” based on viral load results and EOIC processes will be treated as successes. “Probable Failure” & “Definite failure” are defined as a failure.

**Primary analysis of primary outcome:** We plan use of mixed effects logistic regression, accounting for clustering at the facility-level using random effects, to assess the effect of the PCC intervention on treatment success. The main exposure will be exposure to the PCC intervention. To account for potential imbalances due to cluster randomization at baseline and also increase precision, we will adjust for baseline viral suppression (new ART will be assumed to be unsuppressed), care status at enrollment (in care, new ART, LTFU), sex, age, time in care, and randomization strata (initial cluster randomization stratified by facility size and viral load coverage based on programmatic data). Facility clustering will be address through random effects. We will consider including the following potential confounders due to imbalance in randomization: WHO severity groups, marital status and education. We will use standard model diagnostic procedures and consider alternate specifications as needed if we face challenges with standard statistical issues such as model convergence or overfitting. We will use marginal estimation commands to report absolute and relative risk differences under treatment versus control conditions.

In addition to the overall analysis, we will perform stratified analyses to assess changes specifically across:

- Care status (in care, new ART, LTFU) at onset of enrollment
- Baseline viral suppression
- Sex
- Age (<25, 25-44, >45 years)

- Advanced HIV Disease at enrollment in care (WHO Stage 3 or 4, or CD4<200)
- Clinic size and type
- We may assess composite subgroups of age, sex, care status, and suppression status (e.g., Male <25 years old, LTFU not suppressed at baseline) if amenable based on sample sizes.

We will not perform analyses with less than 75 participants.

Sensitivity Analysis of primary outcome: We will perform several sensitivity analyses to ensure the robustness of our results

- Treat “Definite success” as success and everything else as failure (i.e., “probable success” equals failure)
- Treat “probable success” and “probable failure” as missing (i.e., only include definite results)
- Treat viral load<40 and viral load<1000 as “Definite Success”
- Widen the window for viral load to 9 - 21 months.

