### Study design:

We used a stepped wedge cluster randomised trial to assess the effect of the PCC intervention in 24 clinics. We introduced the intervention at four randomly-determined time points at study start, 6, 12 and 18 months. We followed all sites for a total of 24 months. The size of each sequence was not the same, with eight facilities in sequence 1, four in sequence 2, four in sequence 3 and eight in sequence four. The unequal weights allow us to power outcomes such as viral load that occur over periods of time that are longer than each period, and for which cross over would preclude comparison of each treatment condition.

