### **Sample size estimation**

Assuming that 75% of individuals are virally suppressed at baseline and very conservative intraclass correlation between facilities of 0.2, we estimated that we would be able to detect a 10.7% difference between intervention and control arms with 80% power and at  $p<0.05$  if we used approximately 60 patients at each clinic at each of the 16 facilities in waves 1 and 4, for a total maximum of approximately 960 (480 in sequence 1 & 480 sequence 4) viral loads. At each facility, we sought to balance recruitment among new ART starters, individuals who were more than 30 days late (lost or late), and individuals who were in care). The reason for using a sub-cohort is that in we sought to evaluate effects in a “real world” delivery setting, but in these setting outcome ascertainment under routine conditions can be a challenge. By identifying a sub-cohort who are representative of all, but in whom additional data collection at baseline about contact information will allow more intensive outcome ascertainment at the end of the trial to ensure outcome ascertainment.

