## 5.0 – Secondary Outcome – Retention in Care

### 5.1 – In Care at 15 months

**Outcome:** This secondary outcome for retention is being in care at 15 months which will be defined as not being more than 30 days late to a visit at 15 months. We will use EHR data (i.e., SmartCare) that includes sociodemographic, clinical, visit history, and pharmacy data to determine this outcome.

**Population:** The population for this outcome will include all individuals ( $\geq 18$  years old) who made a visit to one of the Wave 1 or Wave 4 study facilities in the first 6 months of the 24-month study period (i.e., period 1). We restrict to facilities in wave 1 and 4 in order to allow a minimum of 15 months of exposure to either the intervention or control conditions at the time out outcome assessment without crossover. This allows us to analyze this aim like a parallel cluster-randomized trial.

|                   | Period 1                                                                                   | Period 2 | Period 3                     | Period 4 | Totals per wave |
|-------------------|--------------------------------------------------------------------------------------------|----------|------------------------------|----------|-----------------|
| Wave 1            | Intervention
All individuals making visit to Facility during Period 1
~40,000 |          | Outcome Ascertainment |          | ~40,000         |
| Wave 2            |                                                                                            |          |                              |          |                 |
| Wave 3            |                                                                                            |          |                              |          |                 |
| Wave 4            | Control
All individuals making visit to Facility during Period 1
~40,000      |          | Outcome Ascertainment |          | ~40,000         |
| Totals per period | ~80,000                                                                                    |          |                              |          | ~80,000         |

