**Analysis:** Time zero will be the first visit a participant makes at a study facility during Period 1. Individuals will be considered to be in care if they are not more than 30 days late at the 15-month time point. We will use mixed effects logistic regression, accounting for clustering at the facility-level using random effects. The main exposure will be exposure to the PCC intervention. To account for potential imbalances due to cluster randomization at baseline and also increase precision, we will adjust for individuals' care status at enrollment (in care, new ART, LTFU), sex, age, time in care, baseline clinic-level retention (i.e., percent of visits where patient was more than 30 days late to their next appointment assessed in the 6 months prior to study start), and randomization strata (initial cluster randomization stratified by facility size and viral load coverage based on programmatic data). Facility will be included as a random effect. We will consider including the following potential

confounders due to imbalance in randomization: WHO severity groups, marital status, and education. We will use standard model diagnostic procedures and consider alternate specifications as needed if we face challenges with standard statistical issues such as model convergence or overfitting. We will use marginal estimation commands to report absolute and relative risk differences under treatment versus control conditions.

In addition to the overall analysis, we will perform stratified analyses to assess changes specifically across:

- Care Status (in care, new ART, LTFU)
- Sex
- Age (<25, 25-44, >45)
- Advanced HIV Disease at enrollment in care (WHO Stage 3 or 4, CD4<200) – Dependent on adequate coverage of CD4 measurements
- Clinic Size and Type
- We may assess composite subgroups of age, sex, and care status (e.g., Male <25 years old, LTFU not suppressed at baseline) if amenable based on sample sizes. We will not perform analyses with less than 500 participants.

**Sensitivity Analysis:** We will perform several sensitivity analyses to ensure the robustness of our results by exploring an alternative definition of 90 days late at the 15-month time point.

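### SAP 3.0 and 5.1 compare 8 with 8 facilities and name no small-cluster inference; a default maximum-likelihood fit with Wald z would give about 8–14% false positives for the primary outcome and 8.5–16% for retention

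*Combined protocol and SAP*

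**What the plan says.** The SAP's study design section describes 24 facilities "with eight facilities in sequence 1, four in sequence 2, four in sequence 3 and eight in sequence four". The primary outcome uses only waves 1 and 4; the SAP 3.0 sample-size paragraph plans about 60 patients "at each clinic at each of the 16 facilities in waves 1 and 4, for a total maximum of approximately 960" viral loads. Under SAP 3.0, Analysis: "We plan use of mixed effects logistic regression, accounting for clustering at the facility-level using random effects".

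SAP 5.1 uses the same 16 facilities for retention, with about 40,000 people per arm. It says of the restriction: "This allows us to analyze this aim like a parallel cluster-randomized trial". Its model is the same: "We will use mixed effects logistic regression, accounting for clustering at the facility-level using random effects".

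Both models adjust for randomisation strata (facility size and viral load coverage; number of strata not given). SAP 5.1 also adjusts for each clinic's retention before the study. Risk differences come from marginal estimation after the fit. Protocol 8.8 says only logistic regression with random effects. Neither document names a degrees-of-freedom method, a small-sample correction, a facility-level test or a permutation test.

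**The concern.** The intervention varies only between facilities, so the test rests on 16 units, however many patients each contributes. At most 14 degrees of freedom (df) remain after the intercept and the intervention. Each stratum term removes one more, and for retention the clinic-level baseline removes another.

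A default mixed logistic fit goes wrong in two ways. Maximum likelihood (ML) underestimates the between-facility variance because it does not allow for the facility-level parameters fitted. The Wald z then treats that variance as known. Both make intervals too narrow and p-values too small. Retention is the most exposed: with about 5,000 people per facility, nearly all the error is between facilities. At stake are the stated 5% level of the primary test and the reading of a retention result whose lower limit is close to zero.

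**Working it through.** **Inputs.** 8 v 8 facilities; 60 per facility (SAP 3.0); about 40,000 / 8 = 5,000 per facility (SAP 5.1); proportion 75% ("Assuming that 75% of individuals are virally suppressed at baseline"). Assumptions: two-sided 5%; 0 to 3 stratum df; intraclass correlation (ICC) 0.02 to 0.2, the top value being the SAP's.

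**The plan's own figure.** SAP 3.0 gives a "10.7% difference between intervention and control arms with 80% power" at an ICC of 0.2. The design effect is 1 + 59 × 0.2 = 12.8, so effective n per arm is 480 / 12.8 = 37.5. The detectable increase is then about 22 points, and power for 10.7 points is 21%. The figure needs an ICC of about 0.021. This is a separate sample-size matter; the error rates below hardly depend on the ICC.

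**Approximate size.** Let ν = 16 minus the fitted facility-level parameters. ML divides the facility-level residual sum of squares by 16 instead of ν, so the Wald statistic is about t(ν) × √(16/ν). Size = P(|t(ν)| > 1.96 × √(ν/16)).
- ν = 14 (no stratum terms): cut-off 1.96 × √(14/16) = 1.83; size 8.8%.
- ν = 11 (3 stratum df): 1.96 × √(11/16) = 1.63; 13.2%.
- ν = 10 (plus the clinic-level baseline): 1.96 × √(10/16) = 1.55; 15.2%.

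With an unbiased variance, z alone would still give 7.0%, 7.6% and 7.8%.

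**Simulation under no effect** (2,000 trials per scenario, ML by adaptive quadrature, Monte Carlo SE about 0.6 points):

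| Setting | Wald z | Likelihood ratio | Facility-level t |
|---|---|---|---|
| Primary, no stratum terms, ICC 0.02–0.2 | 8.7–9.9% | 7.1–8.0% | 4.5–5.9% |
| Primary, 3 stratum df, ICC 0.02–0.2 | 11.3–14.0% | 9.9–12.0% | 5.0–5.6% |
| Retention, no stratum terms, ICC 0.02 and 0.05 | 8.5% | 6.7–6.8% | 4.4–5.1% |
| Retention, 3 stratum df, ICC 0.02 and 0.05 | 13.3–14.0% | 11.3–11.6% | 5.1–5.6% |
| Retention, strata plus clinic baseline, ICC 0.02 | 16.2% | 13.1% | 4.8% |

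A separate simulation of the primary setting (1,200 runs, ICC 0.02–0.05) gave 7.9–8.7% with no stratum terms and 10–13% with three. Replacing z by t(ν) in the ML fit, and nothing else, left 5.9–11.2%.

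**Was z used?** Tables S9 and S12 print intervals and p-values. If both rest on one reference distribution, SE = half-width / critical value, and p follows from estimate / SE.

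| Row | Printed p | z | t, 14 df |
|---|---|---|---|
| S9 male | 0.45 | 0.453 | 0.425 |
| S9 female | 0.22 | 0.215 | 0.197 |
| S9 returner | 0.17 | 0.167 | 0.153 |
| S12 new ART | 0.54 | 0.536 | 0.509 |
| S12 in care | 0.32 | 0.327 | 0.302 |

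Most other rows also favour z. The under-25 rows do not fit: S9 prints 0.003 against 0.019 by z, and S12 prints 0.008 against 0.003.

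**Table S8 retention, 5.9 (0.6 to 11.2).** SE = (11.2 − 0.6) / 3.92 = 2.70; 5.9 / 2.70 = 2.18; p = 0.029 by z. The rescaled columns multiply the SE by √(16/ν).

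| ν | Same SE: p | Same SE: 95% CI | Rescaled SE | Rescaled p | Rescaled 95% CI |
|---|---|---|---|---|---|
| 14 | 0.047 | 0.1 to 11.7 | 2.89 | 0.061 | −0.3 to 12.1 |
| 11 | 0.052 | −0.05 to 11.85 | 3.26 | 0.098 | −1.3 to 13.1 |
| 10 | 0.054 | −0.13 to 11.93 | 3.42 | 0.115 | −1.7 to 13.5 |

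**The case against.** **The SAP does not say ML or Wald z.** A reader might infer that the plan prescribes a test with two to three times the nominal error. It does not; it leaves the inference open. The error rates describe what default software would do. The match of Tables S9 and S12 with z supports that reading for the reference distribution but is silent on how the variance was estimated. A likelihood ratio test would be somewhat better, at about 7–12% for the primary outcome.

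**The upper error rates need three stratum df,** which is an assumption. With no stratum terms the inflation is to about 8–10%. This stands, so the rates must be read as a range.

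**A reader might infer that the retention finding is overturned.** The documents do not support that. Table S8 prints no p-value, so 0.029 is back-calculated. With the same SE, p stays below 0.05 on 14 df. The crossing on 11 df is within rounding: limits of 0.65 and 11.15 give 0.0499, and 0.55 and 11.25 give 0.054. The √(16/ν) rescaling is an approximation, not a re-analysis.

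**A reader might also infer that the primary conclusion changes.** Table S12, the available sensitivity analysis of that outcome, is 0.1 (−9.2 to 9.3), p = 0.99. A wider interval leaves it null.

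**The SAP allows alternative specifications for standard statistical problems.** Its examples are convergence and overfitting, the list is open-ended, and no correction is named. It does not settle the matter.

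**Conclusion.** The concern holds in conditional form. Two 8 v 8 facility comparisons, one of them primary, are planned without any inference suited to 16 clusters. Under default ML with Wald z, type I error is about 8–10% (no stratum terms) to 11–14% (3 stratum df) for the primary outcome. For retention it is about 8.5%, 13–14%, and 15–16% with the clinic-level baseline as well. On that basis the Table S8 retention interval is too narrow and its nominal significance is not secure. That is a statement about uncertainty, not evidence of no effect. The consequence falls mainly on retention; the Table S12 null result is unaffected except for width.

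This rests on three things the documents do not state: the estimation method, the reference distribution and the number of strata. The last is why ν is shown from 14 down to 10.

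**What to change.** In SAP 3.0 and 5.1, state the number of strata and name one method that corrects both the reference distribution and the ML variance bias. Switching from z to t alone is not enough. Take the estimate and its interval from the same analysis, because facilities differ in size and a facility-level interval need not centre on a patient-level estimate. Any of these would serve:
- a strata-adjusted two-stage facility-level analysis, with t on 16 minus the fitted facility-level parameters;
- a permutation test within randomisation strata, with the interval by test inversion;
- a REML-type or pseudo-likelihood mixed model with Kenward-Roger or Satterthwaite df.

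SAP 3.0 allows subgroups down to 75 participants, about 75 / 16 ≈ 5 per facility, where facility proportions are unstable. Use the permutation or df-corrected mixed-model version there.

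The cost is SAP wording, a re-run on existing data and somewhat wider intervals. As results are already tabulated, the re-run should be labelled as specified after the fact.

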| Require Outcome
Adjudication due to no
endline VL (n=150)                                          | Control
(n=73)  | Intervention
(n=77)  |          |
| Silent Transfer                                                                                                   | 15 (20·6)                  | 7 (9·1)                         | 0·044    |
| Official Transfers                                                                                                | 11 (15·1)                  | 10 (13·0)                       | 0·71     |

\*From Chi-square test

**Table S12. Sensitivity analysis for Cohort 4, Effect of PCC Intervention on Treatment Success at 15-months with missing HIV RNA measurements treated as failure (i.e., no outcome adjudication using EOIC algorithm)**

|                                   |            | Control
(n=453) | Intervention
(n=480) |                             |             |
|-----------------------------------|------------|----------------------------|---------------------------------|-----------------------------|-------------|
|                                   | N          | N (%)                      | N (%)                           | Risk Difference
(95% CI) | p-value     |
| Overall                    | 933 | 352 (77.7)          | 368 (76.7)               | 0.1
(-9.2 – 9.3) | 0.99 |
| Baseline Care Status       |            |                            |                                 |                             |             |
| New ART                           | 262        | 85 (66.4)                  | 97 (72.4)                       | 6.0
(-13.0 – 25.0)       | 0.54        |
| In Care                           | 447        | 203 (88.7)                 | 182 (83.5)                      | -4.7
(-14.1 – 4.7)       | 0.32        |
| Returner                          | 224        | 64 (66.7)                  | 89 (69.5)                       | 2.9
(-11.4 – 17.1)       | 0.69        |
| Baseline Viral Suppression |            |                            |                                 |                             |             |
| Suppressed                        | 519        | 226 (86.9)                 | 220 (84.3)                      | -2.0
(-11.5 – 7.5)       | 0.68        |

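### SAP 3.0, 5.1 and 5.2 plan many stratified analyses without an intervention-by-subgroup interaction test, so a difference in effect between subgroups can only be read from separate stratum results

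*Combined protocol and SAP*

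**What the plan says.** SAP 3.0 (Analysis) follows the overall mixed logistic model with stratified analyses by care status (3 levels), baseline suppression (2), sex (2), age (3), advanced HIV disease (2), and clinic size and type (levels not given, at least 2). It then adds: "We may assess composite subgroups of age, sex, care status, and suppression status", subject to sample size. Analyses with fewer than 75 participants are ruled out. The section gives no interaction test, ordering, multiplicity rule or exploratory label for these analyses.

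SAP 5.1 repeats the pattern without the suppression factor ("We may assess composite subgroups of age, sex, and care status") and with a minimum of 500 participants. SAP 5.2 does the same.

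SAP 4.0 (Subgroup analyses) does plan a formal intervention-by-subgroup interaction test for patient experience, but only for subgroups that already appear to differ.

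Table S12 is a sensitivity analysis, "Effect of PCC Intervention on Treatment Success at 15-months with missing HIV RNA measurements treated as failure". It prints a p-value for each of 10 strata and none for interaction. Table S9 (retention in the same 933 people) has the same layout.

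**The concern.** A significant stratum beside a non-significant one does not show that the effect differs between them. The two may differ only in size or noise. The interaction test asks that question directly, and SAP 3.0, 5.1 and 5.2 do not include it. With many overlapping strata and an open number of composites, some stratum will often pass p<0.05 by chance.

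This matters most when the overall result is null, because a stratum can then become the message. Table S12 has that shape: overall 0.1 points (p=0.99), under-25s 24.9 points (p=0.008) on 92 people, or 92/16 ≈ 6 per facility.

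**Working it through.** **1. Stratum count (SAP 3.0).** 3+2+2+3+2+2 = 14 at minimum. If clinic size and clinic type are separate two-level factors, it is 16. SAP 5.1 and 5.2: 3+2+3+2+2 = 12 at minimum.

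**2. The plan's own figure.** The SAP gives no family-wise error figure for subgroups. The only error or power statement for this outcome is in Sample size estimation: "Assuming that 75% of individuals are virally suppressed at baseline", a "very conservative intraclass correlation between facilities of 0.2", and "approximately 60 patients at each clinic at each of the 16 facilities in waves 1 and 4", from which "we would be able to detect a 10.7% difference between intervention and control arms with 80% power". Reproducing it helps to choose ICCs for step 4:
- ICC 0.2: design effect 1 + 59×0.2 = 12.8; effective n per arm 480/12.8 = 37.5; detectable increase 22.1 points; power for 75% vs 85.7% is 21%.
- ICC 0.02: design effect 1 + 59×0.02 = 2.18; effective n per arm 480/2.18 = 220.2; detectable increase 10.6 points; power 80.9%.

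The printed 10.7 points matches an ICC near 0.02, not 0.2. That discrepancy is a separate question. Here it only means that both values should be shown.

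**3. Independence benchmark.** 1 − 0.95^k: 26.5% for k=6, 51.2% for k=14, 56.0% for k=16. These overstate the risk, because the strata overlap and share facilities.

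**4. Simulation allowing for overlap.** No effect anywhere; 16 facilities × 60; 75% success; beta-distributed facility rates; facility-mean t-tests at two-sided 0.05; minimum of 75 applied; 4,000 trials per setting. Care status, sex and age shares approximate Tables S9 and S12. Assumed: 35% advanced disease, two equal clinic groups, no facility-by-stratum variation, and about 14 two-way composites. The 0.05 level is borrowed from the sample-size text.

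| ICC | 14 strata: at least one p<0.05 | Same, given a non-significant overall test | 14 strata plus about 14 composites |
|---|---|---|---|
| 0.02 | 34.5% | 31.2% | 50.5% |
| 0.05 | 27.5% | 24.1% | 45.8% |
| 0.10 | 24.7% | 20.6% | 36.1% |
| 0.20 | 19.3% | 15.1% | 29.3% |

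The single overall test rejected in 4.4% to 5.6% of these trials, so the inflation comes from multiplicity and not from an invalid test. Runs at 80% success gave 34%, 30% and 25% for the 14 strata at ICC 0.02, 0.05 and 0.10, and 19.7% at ICC 0.2.

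**5. What an interaction test would say.** For each factor, SE = (upper − lower)/3.92, w = 1/SE², and Q = Σw(d − d̄)², where d̄ is the weighted mean. Q is referred to chi-square on levels − 1 df.
- Table S12, age: d = 24.9, −6.3, 9.1; SE = 8.27, 4.95, 4.90; d̄ = 5.0; Q = 5.79+5.22+0.70 = 11.7 on 2 df, p = 0.003. The pattern is not monotone in age.
- Table S12, other factors: care status Q = 1.40 (2 df), p = 0.50; suppression Q = 0.17 (1 df), p = 0.68; sex Q = 0.29 (1 df), p = 0.59.
- Table S9, age: d = 25.6, −1.1, 1.1; SE = 10.89, 3.19, 4.97; d̄ = 1.0; Q = 5.5 on 2 df, p = 0.06. The printed under-25 p-value is 0.003.

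These p-values are rough. Strata are treated as independent although they share 16 facilities, and the printed stratum p-values do not match their CIs exactly. In Table S9, 25.6/10.89 = 2.35, which implies p ≈ 0.02 and not 0.003, so part of the gap between 0.003 and 0.06 comes from that mismatch.

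**The case against.** The strongest reply is that the SAP never says a stratum counts as positive at p<0.05. It presents the strata as additions to one overall primary analysis, and it plans to report risk differences. That stands. A reader might infer from the tables that subgroup effects are declared by stratum p-value, but this rests on table format alone. No text in these documents claims a subgroup effect, and the subgroup table for the primary analysis is not among them.

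A reader might also put the chance of a false subgroup finding at a flat 25% to 50%. The documents do not support that. At the SAP's ICC of 0.2 the 14 listed strata give about 20%. The 50% end needs some 14 composites that the SAP only says it may examine. For the 10 strata actually tabulated, the figure is about 27% to 29% at ICC 0.02 and 14% at ICC 0.2. The simulations use unadjusted facility-mean t-tests, not the planned adjusted mixed model, and do not cover SAP 5.1 or 5.2.

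Finally, a reader might take the under-25 result in Table S12 as a chance finding that an interaction test would remove. It would not: the approximate age interaction p of 0.003 times 6 factors is about 0.017, so it would survive a Holm correction.

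What remains is the missing test. SAP 4.0 shows that the authors regard it as the right tool.

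**Conclusion.** The point holds as a gap in method. SAP 3.0, 5.1 and 5.2 plan separate analyses by stratum and provide no test of whether the effect differs between strata. If strata are read at p<0.05, a trial with no effect shows at least one significant stratum among the 14 in about 20% (ICC 0.2) to 34% (ICC 0.02) of cases, and in about 29% to 50% with some 14 composites. These figures apply to SAP 3.0 only and depend on the borrowed 0.05 level and the shares assumed in step 4.

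The choice of rule changes the reading. In Table S9 a striking stratum p-value sits beside a weaker interaction signal. In Table S12 the age signal remains but is non-monotone, and the other three factors show none. Both are sensitivity tables and only illustrate the issue. The overall primary test keeps its error rate.

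**What to change.** In SAP 3.0, 5.1 and 5.2:
- Fit one intervention-by-subgroup interaction per listed factor in the full-cohort mixed model. Do this for every listed factor, not only those that appear to differ.
- Report its p-value beside the stratum estimates and CIs, and base any claim that the effect differs on that test.
- State the levels of clinic size and type.
- Label all subgroup results, composites included, as exploratory.

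The label is needed as well as the test: six interaction tests at 0.05 would still carry up to 1 − 0.95^6 = 26.5% family-wise error if independent. A formal correction such as Holm, removal of stratum p-values, or dropping the composites would be stricter options, but the gap does not require them.

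The cost is a few extra model terms and table columns, with no new data. The downsides are that interaction tests have low power, especially for clinic-level factors with 16 facilities, and that small-stratum p-values can no longer stand alone as findings.

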## 3.0 – Primary Outcome - Treatment Failure

### Study Population:

The population for primary study endpoint will be our treatment failure cohort. This is comprised of a systematic sample of patients who meet the following inclusion criteria at the onset of the study, and for whom we collected additional information to be able to contact them at the end to try and ensure higher levels of outcomes ascertainment. The cohort enrollment was defined by:

- Adult accessing HIV care;
- made a visit to one of the Wave 1 or Wave 4 study facilities in the first 6 months (period 1) of the 24-month study period;
- ever been on ART (including those prescribed on that very visit), not planning on leaving the area, resident of the catchment area of the clinic, and
- we restrict to facilities in wave 1 and 4 in order to allow a minimum of 12 months of exposure the intervention or control conditions at the time out outcome assessment.

At each site the selection of patients for the primary outcome (viral load subcohort) included a quarter new on ART, a quarter lost or late, and half in care.

|                   | Period 1                                                                  | Period 2 | Period 3                     | Period 4 | Totals per wave |
|-------------------|---------------------------------------------------------------------------|----------|------------------------------|----------|-----------------|
| Wave 1            | Intervention
61 patients x 8 facilities =
488 patients total |          | Outcome Ascertainment |          | 488 patients    |
| Wave 2            |                                                                           |          |                              |          |                 |
| Wave 3            |                                                                           |          |                              |          |                 |
| Wave 4            | Control
61 patients x 8 facilities =
488 patients total      |          | Outcome Ascertainment |          | 488 patients    |
| Totals per period | 976 patients                                                              |          |                              |          | 976 patients    |

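### The minimum for clinic size and type subgroups is counted in participants, so it would allow a stratum with one facility per arm, where intervention and facility cannot be separated

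*Combined protocol and SAP*

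**What the plan says.** SAP 3.0 (Analysis) lists "Clinic size and type" among the stratified analyses of the primary outcome. The list ends with one limit: "We will not perform analyses with less than 75 participants".

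SAP 5.1 lists "Clinic Size and Type" for retention at 15 months. Its limit, "We will not perform analyses with less than 500 participants", comes at the end of the bullet on composite subgroups of age, sex and care status. It is unclear whether it applies to the other subgroups.

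Neither section defines the size or type categories or sets a minimum number of facilities. Both handle clustering with a facility random effect and adjust for the randomisation strata, given as facility size and viral load coverage. SAP 5.1 also adjusts for baseline clinic-level retention. Both outcomes are compared between wave 1 and wave 4 facilities only, eight per arm, with no crossover before the outcome is assessed.

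**The concern.** A floor on subgroup size is there to stop unreliable results from being produced. For age, sex or care status, a participant count does this reasonably well, because each subgroup is spread over all 16 facilities. Clinic size and type are different: a stratum is a set of whole facilities, and the randomised information in it is the number of facilities per arm. A floor in participants does not limit that number.

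In the extreme case of one facility per arm, the arm contrast absorbs the whole difference between the two facilities. Nothing is left from which to estimate the facility variance, which would be expected to be fitted at or near zero, and the test then treats patients as independent. The model can converge and give a narrow interval. A statement that the intervention works in one type of clinic could then rest on a single pair of clinics.

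**Working it through.** **Inputs.** Primary cohort: "61 patients x 8 facilities" in each arm (SAP 3.0, Study Population). Retention cohort: about 40,000 per arm over 8 facilities (SAP 5.1), so 40,000 / 8 = 5,000 per facility. ICC and base rate: "very conservative intraclass correlation between facilities of 0.2" and "Assuming that 75% of individuals are virally suppressed at baseline" (SAP 3.0, Sample size estimation).

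**The plan's own figure, to choose a range of ICCs.** The SAP states a detectable difference of 10.7 points at 80% power with "approximately 60 patients at each clinic at each of the 16 facilities in waves 1 and 4".
- At ICC 0.2 the design effect is 1 + 59 × 0.2 = 12.8, the effective size per arm is 480 / 12.8 = 37.5, and a two-sided 5% test of two proportions detects 22.1 points (75% to 97.1%). The stated figure is not reproduced.
- At ICC 0.02 the design effect is 2.18, the effective size is 220, and the detectable difference is 10.6 points.

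That mismatch is a separate matter. It is used here only to show results at both 0.2 and 0.02.

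**Reported intervals as a rough guide to the ICC.**
- Table S12, overall: SE = (9.3 + 9.2) / 3.92 = 4.72 points. The variance without clustering is 0.777 × 0.223 / 453 + 0.767 × 0.233 / 480 = 0.000755. The design effect is 0.0472² / 0.000755 = 2.95. With 933 / 16 = 58.3 per facility, ICC = 1.95 / 57.3 = 0.034.
- Table S8, retention overall: the same steps with 40,000 per arm and an assumed retention of 70% to 80% give about 0.014 to 0.018.

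Both come from adjusted risk differences and are approximate.

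**Does one facility per arm pass the floors?** Primary: 2 × 61 = 122, above 75. Retention: 2 × 5,000 = 10,000, above 500 if that limit applies.

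**Degrees of freedom.** With J facilities per arm, between-facility df = 2J − 2: 0 for one per arm, 2 for two, 6 for four, 14 for all eight, before any facility-level covariate is fitted.

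**Size of the problem with one facility per arm.** With m patients per facility:
- design effect D = 1 + (m − 1) × ICC
- facility share of the variance of the difference = m × ICC / D
- true 95% half-width = 1.96 × √(2 × 0.75 × 0.25 × D / m)
- false-positive rate if clustering is fitted as zero = 2 × (1 − Φ(1.96 / √D))

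ICCs are on the proportion scale. For m = 61:

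| ICC | D | Facility share | Half-width (points) | False-positive rate |
|---|---|---|---|---|
| 0.02 | 2.20 | 1.22 / 2.20 = 55% | 22.8 | 19% |
| 0.034 | 3.04 | 2.07 / 3.04 = 68% | 26.8 | 26% |
| 0.05 | 4.00 | 3.05 / 4.00 = 76% | 30.7 | 33% |
| 0.2 | 13.0 | 12.2 / 13.0 = 94% | 55.4 | 59% |

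Ignoring clustering, the half-width would be 15.4 points at every ICC. The facility share passes one half once ICC exceeds 0.016.

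For m = 5,000 and ICC 0.01: D = 50.99, facility share 50 / 50.99 = 98%, and a false-positive rate of 78% if clustering is fitted as zero. The share only rises with a larger ICC.

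**The case against.** The strongest reply is that this is a worst case that the rule permits, not one that the plan predicts. That stands. The categories are undefined, and no table shows how many facilities fall into each.

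Clinic size also has some protection. The SAP says that randomisation was stratified by facility size, so if the subgroup uses the same classes, each should have facilities in both arms. Type is weaker. Protocol 8.1.2 hopes that stratifying by size and geography will balance facility types, but the SAP records size and viral load coverage as the strata, and neither document uses type as a factor. As an illustration only, protocol 8.4.2 mentions rural, urban, hospital and health post as facility levels. If those four were the types, eight facilities per arm would average two per type, leaving 2 between-facility df. The facility-level covariates would use up some or all of these.

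The clause on diagnostics and alternate specifications for convergence or overfitting might catch a zero-variance fit, but it is generic, and such a fit need not fail to converge.

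A reader might infer that the trial's clinic-type findings are mostly facility noise. The documents do not support this: the supplement's subgroup tables (S4, S8, S9, S12, S13) report no clinic size or type stratum. Nor do they show that two or three facilities per arm would be comparably bad. There the effect can be estimated, and the problem is few degrees of freedom, which the overall model shares to a lesser degree.

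**Conclusion.** The gap is real and should be closed, but it is limited. For clinic size and type, the stated minimum counts the wrong unit and would allow a comparison with no between-facility degrees of freedom. That confounding holds at any ICC. Facility variation dominates the contrast in the retention cohort at any ICC of 0.01 or more (98% or above). In the primary cohort its share depends on the ICC: 94% at the stated 0.2, but only a modest majority (55%) at 0.02, the value that fits the SAP's detectable difference.

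The false-positive rates assume that clustering is fitted as zero, equal facility sizes, a proportion-scale ICC and a normal approximation. The half-widths also assume a 75% base rate.

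The point concerns mainly clinic type, and only SAP 3.0 and 5.1. SAP 4.0 and 5.2 list the same factor but draw on facilities observed both before and after crossover, so these calculations do not carry over. The overall primary analysis is not affected.

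**What to change.** For clinic size and type in SAP 3.0 and 5.1:

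1. Replace the separate stratified models with an intervention-by-stratum term in the full 16-facility mixed model, tested against a t distribution on between-facility degrees of freedom. For a two-level factor that is 16 − 4 = 12, less the facility-level covariates. SAP 4.0 already plans a formal interaction test for subgroups that seem to differ.
2. Define the size and type categories, and report the number of facilities per arm in each.
3. Give no stratum-specific estimate where an arm has only one facility in the stratum. A higher minimum, such as four per arm, would be a matter of preference: with eight per arm, it would let both levels of a two-level factor be shown only under an exact four/four split.
4. Keep the participant floors for patient-level subgroups, and say in 5.1 whether the 500 limit covers all subgroups or only the composite ones.

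The cost is SAP wording, wider intervals for these contrasts, and some clinic-type strata that will not be reported separately.
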